### Strategies for achieving adequate participant enrolment to reach target sample size {15}

To achieve the target sample size, the study will leverage community health workers (ASHAs) to conduct household-based recruitment, ensuring inclusive enrolment of all eligible participants within each cluster from a community-benefit perspective.

### Randomisation sequence generation {16a}

The study will employ simple randomisation at the cluster level and will randomise 18 sub-centres into intervention and control arms.

### Mechanism used to implement the random allocation sequence {16b}

Since randomisation is at cluster level, allocation will be revealed at cluster assignment.

### Whether the personnel who will enrol and those who will assign participants to the interventions will have access to the random allocation sequence {16c}

The allocation sequence will be generated by the statistician; frontline health workers will enrol participants at household level using questionnaires on a tablet PC; randomisation is at cluster (sub-centre) level and interventions delivered at sub-centre by Janakeeya Arogya Kendra (JAK) staff which includes junior health inspectors (JHI), mid-level service provider (MLSP), and junior public health nurses (JPHN).

### Blinding {24}

#### Who will be blinded after assignment to interventions {17a}

The trial is non-blinded. Participants and intervention staff are aware of allocation. Only data analysts will be blinded.

#### If blinded, how blinding will be achieved and description of the similarity of interventions

Participants in the control arm continue with the usual standard of care, while the lifestyle toolkit is implemented in the intervention arm, with each sub-centre (JAK centre) serving as a cluster. Each of the staff including the implementors at the sub-centres is aware of the intervention and in being in the intervention arm, the blinding is only for the data analyst, who is a statistician in this study.

#### If blinded, circumstances under which unblinding is permissible, and procedure for revealing a participant’s allocated intervention during the trial {17b}

Only the data analysts will be blinded. The data analyst will be unblinded if there are any outlier biochemical values which requires immediate action so that the patient can be intimated.

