### Sample size {14}

The sample size was determined using computer-generated randomisation at the cluster level across 18 sub-centres (9 intervention and 9 control).

As this is a type III implementation study, the primary focus will be on evaluating implementation outcomes. In addition, effectiveness will also be assessed based on the following sample size estimation.

To detect a minimum clinically meaningful difference of 0.5% in HbA1c between the two groups, with 80% power, a two-sided alpha of 0.05, and assuming a standard deviation of 1.5% [33], the required sample size under individual randomisation was calculated to be 142 participants per arm.

Given the cluster design, with a planned cluster size of 90 participants and an intracluster correlation coefficient (ICC) assumed to be 0.05, the design effect was calculated as 5.45 using the formula DE = 1 + (m − 1) × ICC. After adjusting for clustering, the required sample size was 774 participants per arm.

The trial will include nine clusters per arm, with 90 participants per cluster (810 participants per arm), which exceeds the minimum required sample size. The fixed cluster size and number of clusters are determined by the structure of the ENDIRA cohort, within which this follow-up study is embedded.

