#### Measurements

Blood sugar and HbA1c would be assessed with self-calibrated point-of-care (POC) devices, and weight and height with digital scales and stadiometers. The above would be measured at baseline and endline and one time-point of 6 months in between using standard procedure. Details of the other patient-reported outcome measures are given in Table 2.

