### Definition of who will be included in each analysis (e.g. all randomised participants), and in which group

Each individual with cardiometabolic multimorbidity who meets the inclusion criteria will be analysed according to the allocation of their cluster on an intention-to-treat basis.

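### The rule that unblinds the data analyst when a biochemical value needs action is unnecessary for its purpose and, under cluster allocation, discloses the arm of at least a whole sub-centre

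*Protocol article*

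**What the plan says.** The Blinding section of the protocol article describes an open trial with one exception: "Participants and intervention staff are aware of allocation. Only data analysts will be blinded". The next paragraph repeats that "the blinding is only for the data analyst, who is a statistician in this study". Item 17b, whose heading concerns revealing a participant's allocated intervention, then sets the condition for breaking that blind: "The data analyst will be unblinded if there are any outlier biochemical values which requires immediate action so that the patient can be intimated".

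Four other places bear on this rule.

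- **Unit of randomisation (item 16a):** "The study will employ simple randomisation at the cluster level and will randomise 18 sub-centres into intervention and control arms". The section defining the analysis groups adds that participants "will be analysed according to the allocation of their cluster on an intention-to-treat basis".
- **Source of the values (Measurements):** "Blood sugar and HbA1c would be assessed with self-calibrated point-of-care (POC) devices". Item 26b on consent for specimens also describes point-of-care testing, but mentions blood sampling only for cardiac patients with type 2 diabetes.
- **Identification (Confidentiality, item 27):** each participant has an individual alphanumeric study ID.
- **Missing data (item 20c):** whether and how to impute will depend on how much is missing and on the assumed mechanism.

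**The concern.** The stated reason for unblinding is to inform a patient. That requires knowing who the patient is. It does not require anyone to know the arm, least of all the one person from whom the arm is being kept.

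In an individually randomised trial, such a disclosure would cost the blind for one record. Here everyone in a sub-centre shares the arm, so the smallest possible disclosure is a whole cluster.

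Masking the analyst protects decisions made after the data are seen. In this plan the clearest example is imputation, which item 20c makes conditional on the data. HbA1c is read by a device, so the analyst's knowledge of the arm cannot alter the measurement. What is at stake is the credibility of analytic choices.

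**Working it through.** **Step 1. Is the arm needed?** Setting the sections side by side:

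- Purpose in item 17b: the patient is to be told of a value. The input needed is identity, which the study ID of item 27 provides.
- The values arise on point-of-care devices, and intervention staff are outside the blind (item 17a). People who may know the arm can therefore act without the analyst learning it.
- Item 21b plans no interim analysis, so nothing else during follow-up calls for the analyst to know the allocation.

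No section gives a reason why the analyst must learn the arm, limits the disclosure to one record, or hands the analysis to a second masked analyst.

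**Step 2. How much does one disclosure reveal?** Item 14 plans 9 clusters per arm with 90 participants each. This gives 9 × 90 = 810 per arm, as stated, and 2 × 810 = 1620 in all. One cluster is 1/18 = 5.6% of the trial. This assumes that the analyst can see which records share a cluster, which the planned multilevel model would require if sub-centre is a level. If the file also carries a masked A/B code, one disclosure decodes all 18 clusters.

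**Step 3. How many clusters might be revealed?** The documents give no rate of actionable values, so the rate r per measurement is an assumption, with values taken as independent. With k measurements per cluster:

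P(cluster revealed) = 1 − (1 − r)^k; expected number revealed = 18 × P.

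*Upper case:* all 90 measured at 0, 6 and 12 months, so k = 90 × 3 = 270 (4860 values in the trial).

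*Lower case:* item 26b mentions HbA1c only for cardiac patients with type 2 diabetes. The only diabetes figure given is 37.3%, in Trial setting (item 9), for cohort members with cardiovascular disease; the share among people with multimorbidity may be higher. Then 0.373 × 90 = 33.6 per cluster. Counting only the two post-baseline visits gives k = 67.1. Baseline is left out because the participant timeline places it before cluster randomisation, although the study implementation text suggests consent comes after it.

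| Assumed r | Upper case, k = 270: P; clusters of 18 | Lower case, k = 67.1: P; clusters of 18 |
|---|---|---|
| 0.1% | 0.237; 4.3 | 0.065; 1.2 |
| 0.5% | 0.742; 13.4 | 0.286; 5.1 |
| 1% | 0.934; 16.8 | 0.491; 8.8 |

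Both columns treat every actionable value as an unblinding of the analyst. If field staff deal with some values before they reach the analyst, the counts fall.

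**The case against.** **The wording may be loose.** The data are de-identified, so the authors may have meant only that an ID is re-linked to a person. That is possible. However, the sentence stands under an item about revealing allocation and uses the word for breaking a blind. If re-linking is meant, the text still needs correcting.

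**The rule may seldom be used.** If the field team sees the value first, few cases would reach the analyst. This stands, and it limits the size. A reader might infer from an assumed 1% rate on 4860 values (about 49 events, or 2.7 per sub-centre) that the analyst would know the arm of most or all sub-centres. The documents do not support that. They give no rate, 4860 is an upper bound in view of item 26b, and not every event need pass through the analyst.

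**Alerts would not necessarily be delayed.** A reader might also infer that abnormal values would reach patients late because they go through the analyst. Item 17b does not say that they go only, or first, by that route, so delay is conjecture and forms no part of this point.

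**The analytic choices may already be fixed.** A statistical analysis plan may exist and is not shown. Covariates and detailed imputation rules are commonly left to it, so it cannot be said that these choices are open. What can be said is that the protocol itself makes imputation depend on the data.

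**The blind may be weak anyway.** Item 16c has the statistician generate the allocation sequence, and the blinded analyst is described as a statistician. A reader might infer that they are the same person and that the blind is void from the start; the documents do not settle this. App access is confined to the intervention arm, so implementation data by site could also show the arm. These points limit what the correction can protect, but they do not justify the rule.

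**Conclusion.** The point holds as a badly fixed rule, not as a missing detail. Item 17b breaks the trial's only blind for a purpose that does not need the arm, and cluster allocation enlarges each disclosure to about 90 participants, or to the whole trial if a masked arm code is used. That conclusion needs no assumed rate, only that the analyst can see cluster membership.

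The cumulative size is uncertain. For rates of 0.1% to 1%, about 4 to 17 of 18 clusters would be revealed on the upper denominator and about 1 to 9 on the lower one. Both ranges assume independent values, and both shrink if field staff intercept values first. The consequence is a needless weakening of analyst masking while data-dependent choices may still be open. It is not bias in the measurements, and it is not a demonstrated loss of the blind across the trial.

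**What to change.** Delete the unblinding rule in item 17b. In its place, state three things:

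- Actionable biochemical values are passed on by study ID, by someone outside the analysis and in the same way in both arms.
- Allocation is not disclosed to the analyst in doing so.
- The analyst stays masked until the models and the missing-data rules are fixed.

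In the same edit, the sponsor could confirm whether the statistician who generates the allocation sequence is a different person from the blinded analyst.

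The cost is a few sentences of text. Sample size and visit schedule are unaffected, and no clinical threshold or action changes.

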### Eligibility criteria for participants {10}

Inclusion criteria: individuals diagnosed with CMM (defined as the presence of two or more of the following conditions: diabetes mellitus, hypertension, stroke, or coronary heart disease); stroke would include a documented ischaemic or haemorrhagic cerebrovascular accident as diagnosed from symptoms or imaging studies; coronary heart disease as defined by individuals with a history of an acute coronary syndrome, or diagnosed coronary artery disease defined as 50% stenosis of one or more of the epicardial coronaries on CT or conventional coronary angiography; or wall motion abnormalities (WMA) on echocardiography or nuclear imaging suggestive of an old myocardial infarction; age ≥ 18 years, providing informed consent for participation and agreeing to follow-up.

Exclusion criteria: individuals with cognitive impairment who are unable to carry out instructions; bedridden individuals; individuals with other significant confounding health conditions additionally like malignancy or chronic airway disease; individuals ≥75 years of age; individuals with a terminal medical condition; pregnant or lactating mothers.

### Participant timeline {13}

**Table Tabb:** 

Timepoint	Trial period				
	Enrolment		Post-randomisation		Close-out
	(−ti to 0)	0	t1 (6 mo)	t2 (12 mo)	tx
Enrolment					
Eligibility screen	X				
Informed consent	X				
Baseline demographics	X				
Cluster randomisation (sub-centres: arm A/arm B)		X			
Intervention/comparator					
Shraddha lifestyle toolkit (arm A)		X			X
Standard of care (arm B)		X	X	X	X
Assessments					
Clinical measures (BP, weight, BMI)	X		X	X	X
Laboratory (HbA1c)	X		X	X	X
Diet (FFQ/calorie tracking)	X		X	X	X
Physical activity (GPAQ)	X		X	X	X
Substance use (WHO-ASSIST)	X		X	X	X
Medication adherence (MMAS-8)	X		X	X	X
Mental stress (PSS-10)	X		X	X	X
Quality of life (EQ-5D-L3)	X		X	X	X
Implementation outcomes (acceptability, adoption, appropriateness, fidelity, cost effectiveness)			X	X	X

Baseline = 0; t1 = 6 months (midline); t2 = 12 months (endline). The arrow indicates continuous delivery of the Shraddha lifestyle toolkit (mHealth messages, JAK visits, yoga sessions) from allocation to endline. Protocol v4 (26 September 2025); IEC ASM-AIMS ECASM-AIMS-2024-001; CTRI/2025/08/092529

## Trial status

Protocol version: v4, dated 26 September 2025.

Ethical approval: IEC ASM-AIMS ECASM-AIMS-2024-001.

Trial registration: Clinical Trial Registry of India (CTRI/2025/08/092529 registered on 06/08/25).

The training for baseline survey is completed, and enrolment will be initiated in the third week of February. The inclusion of the last patient is estimated to be in April 2026. Study close is expected by November 2027.

Each participant will be followed up for 12 months, corresponding to the intervention duration, and the total study duration is 24 months, including formative, implementation, and analysis phases. Primary outcome assessments will be conducted at baseline (0 months), 6 months (midline), and 12 months (endline).

## Implementation aspects

### Intervention and comparator {11}

The intervention consists of a ‘lifestyle toolkit’, called ‘Shraddha’ (means ‘care’ in the local language, Malayalam), that includes guidance on diet and nutrition, tobacco and alcohol cessation, stress management, physical activity, and drug adherence. This toolkit is developed based on the WHO-HEARTS framework with some regional contextualisation. The implementation of the lifestyle toolkit is carried out through community health workers and an m-health platform.

#### Shraddha toolkit development and validation

A rigorous, evidence-based process is undertaken for the development and validation of the Shraddha lifestyle toolkit.Multidisciplinary expert input: Inputs are gathered from experts in various fields, including medical professionals, nutritionists, physical activity specialists, mental health professionals, and cultural experts.Content review: The content undergoes comprehensive iterations for scientific accuracy, cultural appropriateness, and practical relevance.A pilot study is conducted with a small sample of individuals (*n* = 50), diagnosed with cardiometabolic multimorbidity (CMM) from the target region.Participant feedback: Participants are granted access to the toolkit, and their feedback is systematically collected through surveys, interviews, and focus group discussions.Iterative refinement: An iterative feedback loop allows for continuous fine-tuning and refinement of the toolkit based on participant input.Implementation through m-health platform: A digital health platform is established, featuring a two-way communication channel between participants and the study team. Health advice on different components of the toolkit is delivered through a mobile application available on the digital platform. The digital platform disseminates advice on diet and nutrition, tobacco and alcohol cessation, physical activity, medication adherence, and yoga.

#### Patient and public involvement

The co-designing of the toolkit would be through an iterative process involving qualitative interviews and Plan-Do-Study-Act cycles using the Health Belief Model for behavioural change (Table 1).

**Table 1 Tab1:** Qualitative framework for formative phase

Participants	Number of FGDs/IDIs	Themes
Individuals with CMM, both male and female in various age groups	Focus group discussion with individuals in different age groups and gender 2 FGDs—males in the age group 18–60 years 2 FGDs—females in the age group 18–60 years 2 FGDs—males in the age group 60+ years 2 FGD—females in the age group 60+ years Each group will have 8–10 participants	Perception about CMM self-management, medication adherence, and control of hypertension Acceptability of a lifestyle toolkit led to control CMM
Community health workers namely accredited social health activists (ASHAs)	10–12 IDIs with ASHA workers in selected clusters	Barriers and facilitators for control of CMM Perceptions on a lifestyle toolkit to control CMM Opinions on various components to be included in the intervention
Nurses and primary care physicians	10–12 IDIs with nurses and doctors each in selected clusters	Barriers and facilitators for CMM control Perceptions on a lifestyle toolkit to control CMM Feasibility of a lifestyle toolkit intervention to control CMM and the various components that can be included

The Health Belief Model (HBM) serves as the conceptual framework for our study. HBM provides a structured understanding of how patient beliefs and perceptions influence their health behaviours and how the intervention can modify these beliefs to promote better health outcomes. The Shraddha lifestyle intervention is grounded in six core HBM constructs:Perceived susceptibility: Patients of CMM need to understand that they are at a higher risk of recurrence of adverse events such as myocardial infarction, heart failure, or stroke. The Shraddha website will deliver educational broadcasts that highlight the risks associated with poor control of metabolic parameters fostering a sense of urgency for lifestyle changes and adherence to prescribed medications.Perceived severity: If patients believe that the consequences of unmanaged diabetes or hypertension are severe, they may be more likely to engage in preventive behaviours. The Shraddha website will provide videos that illustrate the potential sequences of uncontrolled blood sugar and BP, such as renal failure, vision loss, or cardiovascular events, making the risks more tangible and relatable.Perceived benefits: Success stories and real-life examples of reduced HbA1c levels, BP, and BMI will be shared with participants to reinforce the tangible benefits of their actions. Participants will be able to track improvements in their health indicators (e.g. HbA1c levels, BP, BMI), reinforcing the perceived benefits of the intervention.Perceived barriers: Barriers may include lack of time, difficulty in accessing healthy foods, unavailability of walkways, paths, or fear of side effects from medications. The Shraddha website will provide practical, culturally tailored solutions such as meal plans and simple physical activity suggestions that can be done at home. ASHA workers will offer support during periodic home visits to address any concerns.Cues to action: Reminders and alarms will serve as cues to action, prompting participants to take medications, engage in physical activity, maintain a balanced diet, and avoid tobacco and alcohol.Self-efficacy: The Shraddha website will include features that allow patients to set achievable short-term goals (e.g. taking a 10-min walk each day or avoiding sugar in one meal), track their progress, and receive rewards or recognition for their efforts.

### Eligibility criteria for sites and individuals delivering interventions {10}

The start-line survey assessment would be done by accredited social health activists (ASHAs) at the household, while the Shraddha lifestyle toolkit intervention would be through the sub-centres called JAK (Janakeeya Arogya Kendram), in Kerala. Each of the sub-centres is considered a cluster for randomisation into intervention or control arm. The intervention would be carried out by staff of the JAK team consisting of a JHI, JPHN, and MLSP.

The intervention would be facilitated by a digital health platform with a two-way communication channel between participants and the study team. The developed app (Shraddha) would have modules on the different components of the toolkit accessible on handheld devices of participants. The digital platform will disseminate advice on diet and nutrition, tobacco and alcohol cessation, physical activity, medication adherence, and yoga. The development and validation of the lifestyle toolkit involve a meticulous and evidence-based process. The development phase incorporates inputs from multidisciplinary experts, including medical professionals, nutritionists, physical activity specialists, mental health professionals, and cultural experts. Firstly, experts in the relevant fields reviewed and assessed the content for scientific accuracy, cultural appropriateness, and practical relevance. Secondly, a pilot study will be conducted with a small sample of individuals with CMM from the target regions. The participants will be provided access to the toolkit, and their feedback will be systematically collected through surveys, interviews, and focus group discussions. This iterative feedback loop allowed for fine-tuning and refinement of the toolkit.

#### Components of the toolkit

Diet and nutrition: The lifestyle toolkit includes material that educates individuals about what constitutes a healthy and nutritious diet. It provides information on the foods that should be included in their diet, such as fruits, vegetables, whole grains, lean proteins, and healthy fats. Additionally, the toolkit advises individuals on foods that should be avoided, such as processed and high-sugar foods. Emphasis is placed on consuming a balanced diet that meets their nutritional needs.Physical activity: The lifestyle toolkit emphasises the importance of regular physical activity for individuals with CMM. It encourages participants to exercise at least 150 min each week. This exercise can take various forms, including brisk walking, jogging, stretching exercises, or any other form of physical activity that suits their preferences and health conditions.Stress management: The lifestyle toolkit includes guidance on stress management through yoga practice. Yoga is recommended to reduce stress, improve mental well-being, and enhance overall health. Participants are encouraged to incorporate yoga into their daily routine to cope with stress and promote relaxation.Tobacco and alcohol cessation: For individuals who use tobacco or alcohol, the lifestyle toolkit offers cessation courses to help them quit these harmful habits. The toolkit provides information on the adverse effects of tobacco and alcohol consumption on cardiovascular health and encourages participants to seek support and resources to quit these habits.Adherence to medications: Ensuring adherence to prescribed medications is critical for managing CMM effectively. The lifestyle toolkit provides support and strategies to help individuals stay on track with their medications. This will be achieved through leveraging community health workers and a digital m-health platform, which will offer reminders, educational materials, and personalised guidance to ensure participants take their medications as prescribed.

